#### Bioavailability: first post-isotope clinic

This clinic coincided with the baseline visit for the intervention study. In addition to the blood samples taken for the intervention study afurther fasted blood sample (5 ml, trace element free heparin vacutainer) was taken for the bioavailability study.

#### Bioavailability: second pre-isotope clinic

This clinic coincided with the post intervention clinic of the main study. At this clinic women repeated the labelled iron, meal, and blood sampling regimen described above as well as the blood sampling regimen for the intervention study.

#### Bioavailability: second post isotope clinic (2 weeks after the end of the intervention)

Fasted blood was collected (5 ml, trace element free lithium heparin vacutainer) and transferred into acid washed tubes for the post riboflavin intervention component of the bioavailability study.

### Compliance

The capsules remaining at the end of the study were collected and counted and used as a measure of compliance.

### Power Calculation

There is a lack of consistency in the design of studies that report an improvement in haemoglobin following riboflavin supplementation, in terms of size of dose and duration of intervention and baseline riboflavin and iron status. However, Buzina's study [7] is the most relevant in that the study population was only moderately riboflavin deficient and less so than the subjects we anticipated recruiting. This group showed an increase of 0.7 g/dl Hb over 12 weeks of a modest supplement of 3 mg riboflavin per day.

### Details

We calculated that to achieve a 0.7 g/dl improvement in Hb in a population with an estimated baseline Hb of 13.5 g/dl (SD 1.05) [2] we required 31 subjects per arm of the study. This would give a power of 90%. We aimed to recruit 40 volunteers to each arm, allowing close to 15% dropout.

Based on an expected level of deficiency in this population of 66% it was anticipated that we would need to screen at least 200 young women.

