## Methods/Design

The study design was a randomised, double-blind, placebo-controlled, intervention trial in which participants received one of two daily doses of riboflavin or placebo over a period of eight weeks and effects on measures of iron status and iron handling were evaluated. Ethical approval for the study was granted by the Sheffield University Research Ethics Committee (SMBRER15).

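### The main sample size does not reproduce: with a 0.7 g/dl difference and SD 1.05, 31 women per arm give about 73% power at two-sided 5%, not 90%, and the dropout allowance is 22.5%, not close to 15%

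*Protocol article*

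**What the plan says.** The subsection Details, under Power Calculation, sets the target: "We calculated that to achieve a 0.7 g/dl improvement in Hb". The population has an "estimated baseline Hb of 13.5 g/dl (SD 1.05" g/dl), so 1.05 is given as the spread of haemoglobin at baseline. It concludes that "we required 31 subjects per arm of the study. This would give a power of 90" per cent. On losses it says: "We aimed to recruit 40 volunteers to each arm, allowing close to 15% dropout".

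The section Power Calculation takes the 0.7 g/dl from a cited study whose participants showed "an increase of 0.7 g/dl Hb over 12 weeks". The present trial differs in length; under Methods/Design, "participants received one of two daily doses of riboflavin or placebo over a period of eight weeks".

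The main calculation gives no significance level, sidedness, test, SD of change or baseline correlation. The separate calculation for the bioavailability arm uses 0.05. Data Analysis plans ANOVA across the randomised groups, followed where significant by a Scheffe or a Kruskal-Wallis multiple-comparison test, and mentions no baseline adjustment.

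**The concern.** Difference, SD, number per arm and power are all printed, so the reader can check them against each other, and they do not agree. The dropout percentage does not link 31 to 40 either.

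Haemoglobin is one of several primary outcome variables and the only one with a sample-size calculation for the main study. A reader who takes the 90% at face value would put the chance of missing a true 0.7 g/dl difference at 10%. On the printed inputs it is about 27% at 31 per arm and about 16% at 40 per arm. A null haemoglobin result would then carry less weight than the stated power suggests.

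**Working it through.** **Inputs.** Difference δ = 0.7 g/dl, SD σ = 1.05 g/dl, n = 31 per arm, power 90%, 40 recruited per arm, dropout close to 15% (all from Details). Three arms, equal allocation (Randomisation to treatment). Assumption: two-sided α = 0.05, because the main calculation gives none.

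**1. Number needed for 90%.** Standardised effect = 0.7/1.05 = 0.667. By normal approximation

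n = 2 (z₀.₉₇₅ + z₀.₉₀)² (σ/δ)² = 2 × (1.960 + 1.282)² × 1.5² = 47.3, so 48 per arm.

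The t-test (noncentral t) needs 49. The plan's 31 is not reproduced.

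**2. Power at 31.** Noncentrality = 0.7/(1.05 × √(2/31)) = 2.625. Normal approximation: Φ(2.625 − 1.960) = 74.7%. Noncentral t on 60 degrees of freedom: 73.3%.

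**3. Other readings tried, to see whether 31 at 90% can be recovered.**

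| Reading | Power at 31 per arm | n per arm for 90% |
|---|---|---|
| Two-sample t, two-sided 5% | 73.3% | 49 |
| Two-sample t, one-sided 5% | 82.9% | 40 |
| Three-group ANOVA, means 0, 0.7, 0.7 | 76.5% | 44 |
| Three-group ANOVA, means 0, 0.35, 0.7 | 63.2% | 58 |
| Both doses pooled 2:1 against placebo | 85% | 36 in placebo arm (normal) |
| Within-arm paired test, SD 1.05 | 94.9% | 26 |

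None gives 31 at 90%. That combination appears only with inputs that the article does not state:

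- Covariance analysis with baseline correlation r: σ becomes 1.05 × √(1 − r²). At r = 0.6 this is 0.84, n = 31 by normal approximation, and t-test power at 31 is 89.8%.
- Change score: σ becomes 1.05 × √(2(1 − r)). At r = 0.68 this is again 0.84, with the same power; at r = 0.7 it is 91.5%.
- An SD of about 0.85 in place of 1.05.
- One-sided α of 0.10: n = 30, and 91.0% at 31 by normal approximation.

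**4. Dropout.** This does not depend on α.

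- From 40 to 31: 1 − 31/40 = 22.5%.
- 31 allowing 15% loss: 31/0.85 = 36.5, so 37.
- 40 after 15% loss: 40 × 0.85 = 34.

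**5. Power at the sizes that matter** (one dose against placebo, two-sided 5%, t-test, no multiplicity correction). At 34: 77.3%. At 40: 83.8%. Initial Findings reports 123 women randomised and 4 not completing; (123 − 4)/3 = 39.7 per arm, with 83.4%. The difference detectable with 90% power is 0.88 g/dl at 31 and 0.77 g/dl at 40.

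**6. Scheffe pairwise comparison.** The critical value is √(2 × F₀.₉₅; 2, 3n − 3). At n = 40 it is 2.48, with noncentrality 0.7/(1.05 × √(2/40)) = 2.98, and power is about 69%. At 49 per arm it is about 79%.

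**The case against.** The best defence is that the main calculation is silent on level, sidedness and test, and that 1.05 is a baseline SD while the target is an improvement in a trial that measures haemoglobin at weeks 0 and 8. A baseline-adjusted analysis with a correlation near 0.6, or a change score with nearly 0.7, would support 31 per arm. This stands as a possible origin of the figure, so I do not say that 31 could never be right. It does not rescue the text as printed: no correlation is given, and Data Analysis names ANOVA without adjustment.

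It is also fair that the dropout slip errs in the safe direction, since 40 exceeds the 37 needed to keep 31, and that actual loss was small (4/123 = 3.3%). The trial is complete, so the 84% at about 40 per arm describes it better than the 73% at 31. But the article attaches its 90% to 31, and at two-sided 5% even 40 does not reach it. At one-sided 5%, 40 would (90.5%), but no one-sided test is stated.

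Two stronger readings are tempting and not supported. A reader might infer that 0.7 g/dl is a rise within one group, wrongly used as a between-group difference. Background lists the cited source among randomised controlled trials, and the article does not say whether the figure is net of control. A reader might also scale the 12-week effect down to 8 weeks and quote a much lower power. The documents say nothing about how the effect builds up over time, and Power Calculation describes the cited population as less deficient than the women to be recruited. The difference in duration is a caveat and no more.

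**Conclusion.** The point holds in this form: the printed difference, SD and number per arm do not yield the printed power. At two-sided 5%, for one dose against placebo with an unadjusted t-test, 31 per arm give about 73%, a shortfall of about 17 percentage points, and 90% would need 49 per arm, which is 18 more. One-sided 5% narrows the gap but does not close it. The two-sided 5% level is my assumption for the main calculation.

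The mismatch between 22.5% and close to 15% is certain whatever the test, but minor in effect. The documents do not show that the trial as run is severely underpowered; its power for 0.7 g/dl is about 84% for an uncorrected pairwise t-test and about 69% for a Scheffe comparison.

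**What to change.** - Restate the power for 0.7 g/dl and SD 1.05 as about 73% at 31 per arm and about 84% at the roughly 40 per arm who completed, for one dose against placebo at two-sided 5% without multiplicity correction. Say that 90% would have needed 49 per arm on that basis.
- Add that power is lower, about 69% at 40 per arm, for a Scheffe pairwise comparison, so that the figure matches the planned follow-up test.
- Give the dropout allowance from 40 to 31 as 22.5%.
- If 31 came from a baseline-adjusted or change-score calculation, state the assumed correlation (about 0.6 or nearly 0.7 respectively) and name that analysis under Data Analysis.
- Note that the 0.7 g/dl was seen over 12 weeks while this trial treats for eight.

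This costs a few sentences and no participants. The stated power becomes less favourable. If the correlation route applies, the analysis must match it; haemoglobin at both time points is already collected.

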#### Power calculation for the bioavailability

It was estimated that 15 subjects per group would be required to detect a 5% difference between the 4 mg and placebo intervention groups in iron incorporation into erythrocytes in response to intervention. This estimate was based on a mean bioavailabilty of 15% and a SD of 5% [9]with a power of 90% and a significance level of 0.05.

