### Initial Findings

#### Recruitment

Over a period of fifteen months, 256 women were screened for moderate riboflavin deficiency. From this initial screening, 145 were eligible for the intervention trial on the basis of an EGRAC>1.40. This represented 57% of our screened population. Of these 123 women agreed to take part in the main study (36 of these were randomly allocated to the bioavailability arm). In all, 4 women failed to complete the main study (none of whom, were in the bioavailability arm).

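### The bioavailability sample size of 15 per group at 90% power does not follow from its own inputs, which give about 75% two-sided; actual power depends on which SD is meant

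*Protocol article*

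**What the plan says.** The section on the power calculation for the bioavailability arm gives the result and its inputs together: "It was estimated that 15 subjects per group would be required to detect a 5% difference between the 4 mg and placebo intervention groups". The outcome is the incorporation of iron into red cells as a response to the intervention. The basis is stated as "This estimate was based on a mean bioavailabilty of 15% and a SD of 5"%, taken from a cited source, "with a power of 90% and a significance level of 0.05". The section does not state sidedness, label the SD, or give a within-woman correlation.

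The sections on the bioavailability clinics describe two isotope measurements per woman: one dosed two weeks before the intervention starts, and one dosed at its end and read two weeks later. The section on bioavailability data analysis names linear regression and ANOVA models at P < 0.05, without saying whether the earlier measurement enters the model.

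On numbers achieved, the Recruitment part of Initial Findings reports that "36 of these were randomly allocated to the bioavailability arm", and the Abstract says that all 36 completed. The division of the 36 between 4 mg and placebo is not given.

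**The concern.** There are two separate problems, and they should not be merged.

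The first is arithmetic. A difference of 5 with an SD of 5 is a standardised effect of 1.0, and 15 per group is visibly too few for 90% power at that effect size with a two-sided 0.05 test.

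The second is the meaning of the SD. The contrast is a response to intervention measured before and after in each woman. The SD is printed next to the mean level of bioavailability, which suggests the spread of a single measurement. If so, the variance of the analysed quantity depends on the correlation between a woman's two measurements, which the article does not give.

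This arm is the trial's direct measurement of iron absorption or utilisation. A reader faced with a null result will judge how much it excludes partly by the stated 90%, so that figure should be one the inputs support.

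**Working it through.** **Inputs** (all from the section on the bioavailability power calculation unless noted)
- Difference: 5 percentage points, read as absolute. The relative reading (5% of 15 = 0.75 points) would need 934 per group, so it cannot be meant.
- SD: 5 percentage points.
- Power 90%, alpha 0.05. Two-sided is assumed; one-sided is also tried.
- Two groups of 15. For the women obtained, 36 in total (Recruitment, under Initial Findings), taken as 18/18 by assumption.

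**Step 1. Try to reproduce 15 per group**

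n per group = 2 × (z₁₋α/₂ + z₁₋β)² × (SD/difference)² = 2 × (1.960 + 1.282)² × (5/5)² = 21.0, so 22 per group. The t-test calculation gives 22.02, so 23.

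Other readings tried:

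| Reading | n per group required |
|---|---|
| Two-sided, 90% power | 22 (normal), 23 (t) |
| One-sided, 90% power | 18 |
| Two-sided, 80% power | 16 (normal), 17 (t) |
| One-sample or paired formula, 90% power | 11 (normal), 13 (t), but the stated contrast is between two groups |

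None returns 15. The nearest is two-sided at 80% power, and 15 falls slightly short of that too.

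**Step 2. Power if 5% is the SD of the analysed quantity** (noncentral t)

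| Per group | Two-sided | One-sided |
|---|---|---|
| 15 | 75.3% (normal approximation 78.2%) | 84.8% |
| 18 | 83.0% (normal approximation 85.1%) | 90.2% |
| 23 | 91.2% | – |

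The difference detectable with 90% power, two-sided, is about 6.1 points at 15 per group and 5.6 points at 18 per group.

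**Step 3. Power if 5% is the SD of a single measurement**

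Let r be the correlation between a woman's two measurements. It is not given in the article, so r = 0 to 0.7 is an assumed range.
- Change score: SD = 5 × √(2(1 − r))
- ANCOVA on the pre-intervention value: residual SD = 5 × √(1 − r²)

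Two-sided power for a 5-point difference (noncentral t):

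| r | Change score SD | n = 15 | n = 18 | ANCOVA SD | n = 15 | n = 18 |
|---|---|---|---|---|---|---|
| 0 | 7.07 | 46% | 54% | 5.00 | 75% | 83% |
| 0.3 | 5.92 | 61% | 69% | 4.77 | 79% | 86% |
| 0.5 | 5.00 | 75% | 83% | 4.33 | 86% | 92% |
| 0.6 | 4.47 | 84% | 90% | 4.00 | 91% | 95% |
| 0.7 | 3.87 | 93% | 96% | 3.57 | 96% | 98% |

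**Step 4. What would make the stated figure true**

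For 15 per group to have 90% power, the SD of the analysed quantity must be about 4.08.
- Change score: r = 1 − (4.08/5)²/2 ≈ 0.67
- ANCOVA: r = √(1 − (4.08/5)²) ≈ 0.58

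The article states neither value.

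**The case against.** The best defence is that 15 per group may have been adequate. If 5% is the spread of a single measurement and a woman's two measurements correlate at about 0.67 (change score) or 0.58 (baseline-adjusted), the stated 90% is correct. A journal article may leave the correlation, the sidedness and the exact model to a fuller document, and the named regression models do not exclude a baseline covariate. This stands as a reason not to call the design underpowered. It does not rescue the printed calculation, which offers its inputs as the basis for 15, and they do not give 15.

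Three stronger readings are tempting, and the documents do not support them.
- A reader might infer that the arm's true power is 75%. That holds only if 5% is the SD of the analysed quantity, which for a change score means r = 0.5.
- A reader might take it as established that the SD is between-subject. Its placement beside the mean suggests so, but the article does not label it and its source is not available here.
- A reader might conclude that a true 5-point effect would be missed one time in four. That uses 30 women, but 36 completed. With an even split, the miss rate on the stated SD is about 17%, or one in six.

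It can also be said that this is a subgroup arm, that iron incorporation is not among the listed primary outcome variables, and that recruitment is over. All of that stands and bears on severity.

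**Conclusion.** The statement of 15 per group at 90% power is wrong on its own inputs. Two-sided at 0.05, they require 22 to 23 per group; 15 gives about 75% and an even 18/18 split about 83%. One-sided testing raises 15 per group only to 85%. These figures rest on an absolute 5-point difference and on 5% being the SD of the analysed quantity.

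Whether the arm was in fact short of 90% power cannot be settled from the article. If the SD is that of a single measurement, the answer turns on r, and it could fall well below 75% or exceed 90%. The 36 completers soften the shortfall on the stated inputs without removing it in a two-sided test. Severity is moderate: the printed justification needs correcting and the SD needs identifying, but the trial's listed primary outcomes do not depend on it.

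**What to change.** 1. Restate the power on the stated inputs: about 75% at 15 per group and about 83% at 18 per group, two-sided. Alternatively, give the difference detectable with 90% power, about 6.1 and 5.6 points respectively. Report the actual split of the 36 women and use it.
2. State the sidedness, and say whether 5% is the SD of a single measurement or of the change.
3. Name the comparison as ANCOVA of post-intervention incorporation on the pre-intervention value, and quote power for that model over a stated range of r. If 5% is the single-measurement SD, r = 0.5 gives about 86% at 15 and 92% at 18 per group. Do not quote 23 per group as the requirement for this model, because that figure applies only when r is near 0.

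The cost is wording plus one covariate that has already been measured. No extra participants or samples are needed. The article describes the statistical analysis as still under way, so the model can be fixed in writing now, with the date and the state of unblinding recorded.

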### Dietary Analysis

To evaluate any dietary changes during the intervention, volunteers were asked to complete a four-day food diary before the baseline visit and again before the interim visit. The four days included one weekend day. The diary was sent to the participant prior to the first visit and then discussed with the researcher at the first visit for checking legibility, correct entry of food types and portion sizes. The second diary was given at this visit for completion prior to the next interim visit and the instructions explained again if necessary.

The diaries were developed by the Institute of Food Research, Norwich and modified to include sufficiently detailed instructions as to make them self-explanatory. Food portion booklets based on the former Ministry of Agriculture, Fisheries and Food (MAFF) food atlas [10] were also provided to assist with estimating portion sizes. The data from the food diaries were analysed for micronutrient and macronutrient content using Windiets Research software (Robert Gordon University, UK).

### Blood collection and laboratory analysis

Blood was collected for the screening and interim visits by finger prick sampling (500 μl).

Immediately following the clinics, blood samples were taken to the laboratory, separated by centrifugation and the red cells washed with PBS and lysed with an equal volume of water. Haemolysates were stored at -20°C for the assessment of riboflavin status using the EGRAC assay. Plasma was stored at -20°C for ferritin analysis.

At the baseline and post intervention visits, blood was collected by venupuncture into vacutainers. A 10 ml blood sample was collected into EDTA tubes and separated by centrifugation into plasma and red cells. The red cells were washed and haemolysed for EGRAC measurement as before and the plasma divided into aliquots and stored at -80°C for the measurement of other variables. A further 5 ml blood were collected into a separate EDTA tube and sent to the Haematology Department at the Royal Hallamshire Hospital for full blood count and zinc protoporphyrin (ZPP) measurements.

At the follow up visit a single 5 ml sample was collected into EDTA tubes for EGRAC and plasma ferritin measurements.

For the bioavailability arm of the study a further 5 ml blood were collected at the times described in the bioavailability protocol, into heparin trace-element free tubes and the whole blood aliquoted into 4 acid washed microfuge tubes for sending to the Institute of Food Research, Norwich for isotopic analysis.

### Outcome Variables

#### Primary Outcome Variables

To assess haematological parameters the following were measured in the haematology laboratory at the Royal Hallamshire Hospital, Sheffield: red blood cell count, PCV, MCV, MCHC, haemoglobin and ZPP. ELISA kits were used to measure plasma ferritin (Spectro Ferritin Kit, ATi Atlas Ltd. Chichester, UK) and plasma soluble transferrin receptor (Quantikine DTFR1 – Human sTfR Immunoassay, R&D Systems, Abingdon, UK)

Riboflavin status was measured by the EGRAC assay [5] and plasma flavin concentration measured using an HPLC kit method (Chromsystems, Munich, Germany).

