### Data Analysis

For descriptive statistics baseline values will be analysed according to randomisation group. Data will be tested for normality using Shapiro-Wilk and Kolmogorov-Smirnov tests. Categorical variables will be tested using the Chi squared test and continuous variables compared across randomisation groups using ANOVA.

The effects of intervention on all continuous variables will be analysed by ANOVA. Where ANOVA indicates a significant difference across the randomisation groups a Scheffe test or Kruskal-Wallis Multiple Comparison Z-value test will be carried out, as appropriate, to identify where the differences lie.

Spearman Rank Correlations will be conducted to examine possible associations between selected continuous variables.

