### Bioavailability data analysis

Statistical analysis will be performed at IFR using R data analysis software [14]. Standard Linear Regression and ANOVA models will be used. For all models, regression diagnostics will be checked to determine if data transformations, outlier omissions or alternative non-parametric models are required. Results will be considered significant if P < 0.05 for all tests.

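### Ten unranked variables are called primary and each has its own ANOVA with no control across them, although the main trial was sized on haemoglobin alone

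*Protocol article*

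**What the plan says.** The section Primary Outcome Variables of the protocol article lists, in this order:

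- six haematology laboratory measures: "red blood cell count, PCV, MCV, MCHC, haemoglobin and ZPP";
- two iron markers: "ELISA kits were used to measure plasma ferritin", and the same sentence adds "plasma soluble transferrin receptor";
- two measures of riboflavin status: "Riboflavin status was measured by the EGRAC assay [5] and plasma flavin concentration measured using an HPLC kit method".

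That makes eight haematological or iron variables and two riboflavin-status variables. The section puts none ahead of the others.

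Data Analysis then states: "The effects of intervention on all continuous variables will be analysed by ANOVA". The follow-up step is: "Where ANOVA indicates a significant difference across the randomisation groups a Scheffe test or Kruskal-Wallis Multiple Comparison Z-value test will be carried out". That step locates differences between the three arms for one variable at a time. Nothing in the section operates across variables.

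The Details under Power Calculation size the main trial on one variable: "to achieve a 0.7 g/dl improvement in Hb in a population with an estimated baseline Hb of 13.5 g/dl". A significance level appears only under Bioavailability data analysis: "Results will be considered significant if P < 0.05 for all tests".

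**The concern.** The sample size treats haemoglobin as the deciding variable, while the outcome list treats ten variables as equals. The document does not say which variable, or how many, must differ before an effect on haematological status is concluded. With eight separate tests bearing on that conclusion, a chance finding in any one of them can be reported as a significant primary outcome.

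This matters because the Discussion section ties a demonstrated effect to reconsidering the EGRAC threshold for deficiency, without defining what such an effect would be. The two riboflavin-status variables add a second difficulty. They sit under the same primary heading and would be expected to respond to a riboflavin supplement whether or not iron status changes. A significant result on either one says nothing about haematology.

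**Working it through.** **The plan's own figure.** The document gives no error rate across outcomes. The only related figure is 31 per arm at 90% power for haemoglobin. With a difference of 0.7 g/dl, SD 1.05 and a two-sided 5% level, n = 2 × (1.960 + 1.282)² × (1.05/0.7)² = 2 × 10.51 × 2.25 = 47.3, so 48 per arm. The stated 31 is not reproduced. That is a separate matter and does not enter the error rates below. What counts here is that only haemoglobin was used.

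**Inputs.**
- Eight variables, from Primary Outcome Variables, leaving out EGRAC and plasma flavin.
- Three arms of 40: the recruitment target, and close to the 119/3 = 39.7 completers per arm.
- Level 0.05 per ANOVA: an assumption for the main trial.
- Pairwise correlations of 0 to 0.7: an assumption, since the document gives none.
- One test per variable. Ferritin is also sampled at weeks 4 and 12, and those tests are not counted.

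**Any significant ANOVA under no effect.** If independent, 1 − 0.95⁸ = 0.337. For all ten variables it would be 1 − 0.95¹⁰ = 0.401, but the two riboflavin measures do not belong in a haematological error rate.

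**After the Scheffé step.** With 2 and 117 degrees of freedom the 5% point of F is 3.07, so a pair of arms differs when |t| exceeds √(2 × 3.07) = 2.48. Simulating one variable gives a false dose-versus-placebo difference in about 2.8% of trials, and about 1.4% in one stated direction. Over eight independent variables, 1 − (1 − 0.028)⁸ = 0.20 and 1 − (1 − 0.014)⁸ = 0.11.

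**With correlation.** Simulation of eight equally correlated normal outcomes, each oriented so that a positive difference is favourable:

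| Pairwise correlation | Any significant ANOVA | Any dose-versus-placebo difference (Scheffé) | Favourable direction only |
|---|---|---|---|
| 0 | 33–34% | 20% | 10–11% |
| 0.3 | 30% | 18% | 9% |
| 0.5 | 26% | 16% | 8% |
| 0.7 | 20% | 12% | 6% |
| One variable alone | 5% | about 2.8% | about 1.4% |

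**Sensitivity.** The red cell indices are linked by arithmetic: mean cell volume is packed cell volume over red cell count, and MCHC is haemoglobin over packed cell volume. A model that keeps these links and adds a shared iron factor of varying strength gives 20–29% for any significant ANOVA. At an equal correlation of 0.8 the figure is 17%. The Kruskal-Wallis alternative was not simulated.

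**The case against.** The strongest case on the other side has four parts.

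1. **The large figure is not the risk of a false benefit claim.** A reader might infer that riboflavin would be falsely said to improve haematological status in up to a third of such trials. The document does not support that. The 20–34% includes differences between the two doses and differences in the unfavourable direction, and it stops before the planned Scheffé step. This part stands. The rates after that step are the ones nearest to the claim.

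2. **EGRAC and plasma flavin are legitimate outcomes.** A reader might infer that they only show the capsules were taken, or that listing them makes a positive trial close to certain. Neither follows. Objectives includes riboflavin status, two doses are compared, and compliance has its own measure in capsule counts. Nothing says that one significant variable, or a change in EGRAC, would establish a haematological effect. This part also stands. What remains is that they cannot be evidence for that effect.

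3. **Adjustment may be set out elsewhere.** An adjustment method can properly be left to an analysis plan, and that plan is not shown. This covers the method but not the designation of primary outcomes, which this document makes itself.

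4. **A broad list fits the aim.** Study Aim asks for a wide range of haematological measures. Keeping all eight with an adjustment would serve that aim too, so a single primary is not the only sound remedy.

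**Conclusion.** The point holds for the eight haematological and iron variables. The document names them all as primary, ranks none, tests each separately and sizes the trial on one. Under the assumed 5% level and correlations of 0 to 0.7, the chance of a false significant ANOVA is about 20–34% against 5% for one variable. The upper end requires independence, which the arithmetic links between the red cell indices rule out, so the lower part of the range is more plausible. A false dose-versus-placebo difference after Scheffé has a chance of about 12–20%, and about 6–11% counting only the favourable direction. For one variable these are about 2.8% and 1.4%.

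The size depends on a level that the document states only for the bioavailability analysis and on correlations it does not give. The direction of the problem does not depend on either: unless the variables are perfectly correlated, eight unadjusted tests carry more error than one.

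**What to change.** **If treatment codes have not been linked to results:** name week-8 haemoglobin, the variable the trial was sized on, as the single primary haematological outcome. Report the other seven haematological and iron variables as secondary, with Holm-adjusted p values.

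**If they have been linked:** the Discussion section says the analysis is underway, and choosing one primary after seeing results would not be credible. In that case say so, report all eight with Holm adjustment, and do not claim success on a selected one.

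**In either case:** keep EGRAC and plasma flavin as outcomes for the riboflavin-status objective, and state that they do not count as evidence of a haematological effect.

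**Cost.** No new data are needed, since haemoglobin is already measured at baseline and week 8. There is a loss of power for the individual variables other than haemoglobin. Holm multiplies the smallest p value by 7 with seven secondaries, so it must fall below 0.05/7 = 0.0071. With all eight the factor is 8 and the threshold 0.05/8 = 0.00625, and haemoglobin then shares that loss.
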